### Report Design Specifications

Report generation, specifically the report structure and visual content, is essential to help clinicians with decision-making. It shall be easily understandable by inexperienced TDM pharmacologists. The displayed information must be carefully selected and structured to not lose the prescriber with a too complex presentation and terminology [23]. It should contain the appropriate information presented visually. In addition, alerts shall be issued, if necessary, in a form following the Instrument for Evaluating Human Factors Principles in Medication-Related Decision Support Alerts (I-MeDeSa) principles [24].

The definition of the report layout will be elaborated through the following process. We will prepare mock reports showing various layouts based on use cases. The designs will be done after reviewing the literature to identify good practices. We will then, in Tanzania, expose a cohort of clinicians to these reports and collect their input through semistructured interviews. We expect to reach 10 clinicians from different facilities, in Tanzania. We also aim to ask 10 non-Tanzanian clinicians to obtain helpful information about varying preferences regarding information representation depending on culture or background. Thus, pharmacologists with strong expertise in dosage adjustment will be included to get their specific needs compared to general medical doctors. We will improve the report’s rendering over 2 cycles of interviews, with thorough attention to the clinicians’ feedback. The output of this study will allow for the design of the final report. This study will also illustrate the differences between TDM expert pharmacologists and general medical doctors and, hopefully, between other countries and Tanzania for report design acceptance.

The research question components are as follows: (1) What information and how this information shall be displayed to clinicians for an efficient decision-making process concerning dosing regimen? (2) What are the differences in terms of expectations about reports data and design among expert pharmacologists and medical doctors, both in Tanzania and the Western world?

### CDSS

Tucuxi offers a GUI, graphs with drug concentration predictions surrounded by percentiles, and dosage adaptation propositions. The software uses Bayesian inference to find the most likely individual parameters integrating information from the underlying popPK model and the observations obtained on the patient. Currently, the user has to decide by himself or herself on the dosage adjustment among those proposed by the software and write some sentences to fill up a report. Experienced pharmacologists do this manually, but this practice requires particular skills related to this specialized medical discipline. Clinicians who make final decisions about the drug dosage rely on monographs, experience, or a consultation with a pharmacologist for dosage adaptation. In that context, a CDSS can bring much-needed information to decision makers [25] in locations where expert pharmacologists are not readily available.

The CDSS that will be developed in TuberXpert will offer various features and they are (1) assess the expectedness (likelihood) of a drug concentration result, taking into account the patient’s characteristics; (2) assess the adequateness (target attainment) of the current dosage; (3) propose a dosage adjustment if required; (4) present clear and meaningful messages within the report to help the clinician with the decision-making process; and (5) generate alerts when data seem suspicious or erroneous.

While the current Tucuxi software allows the necessary computations, this project will add a new level to the computing engine. Research is needed to ensure the system is extensible enough to address other medical drugs without colossal refactoring. Therefore, a perfect balance between genericity and rifampicin-specific features has to be found. The system must also be easily integrated into existing IT systems thanks to a generic interface. It will also need to be highly reliable and deployable in the field.

Common and uncommon use cases (eg, type of patient, under or over drug exposure, and standard or strange observed drug level) will be identified in both Switzerland and Tanzania, to increase case heterogeneity. Indeed, the patients with TB treated in Switzerland are usually exceptional cases compared to the daily routine patients with TB in Tanzania. Artificial use cases will complete this panel to cover as many borderline cases as possible. We will carefully analyze every patient and use case scenario to design a formal decision tree [26] that will lead to software development. This decision tree will be required to create the software and will be published as a guide for clinicians doing the job by hand. Special attention will be given to appropriate corrective actions [27]. For instance, if a measured drug level appears out of range, an alert shall identify either a potential error in the data or a lack of adherence whenever such sources of bias can be identified with sufficient certainty. In less clear situations, an estimation of the likelihood of common artifacts versus a definite individual PK alteration in the patient should be issued.

The report to be generated shall display proper values and graphs and offer readable sentences. In close relation with the decision tree, a set of standard customizable sentences will have to be defined. They will then be integrated to offer medically meaningful reports as if a human professional had written them. These sentences will be related to TB and rifampicin. Still, the software will be developed keeping in mind that it should be straightforward to define new sentences for other diseases and medicinal drugs. Thanks to established configurations, the core components will be generic, and a parametrization will enable repurposing as efficiently as possible.

We will conduct a short survey in Tanzania to address the availability of computer infrastructures, printers, and connectivity in clinics and at the doctor’s desk. We also will ensure that the system can be connected to the laboratory information system that manages the transmission of drug concentration measurement results. In addition, having a version of the CDSS where computations are running remotely could be an option if the clinicians in the field do not own computers with enough computing power. If this approach is required, the patient’s data could stay on the clinician’s computer to ensure data privacy.

The research question components are as follows: (1) What data processing leads to the most accurate suggestions based on the available data of a specific patient? (2) What setup is most appropriate for rural clinics where access to computer infrastructures is not ideal?

### System Validation

TuberXpert will then be validated after the CDSS and report generation are completed, considering the rifampicin popPK model has already been validated and calibrated to the target population. We will assess the correctness of the generated reports based on use cases designed within the project among patients on rifampicin followed at CHUV and on the data gathered in Tanzania (retrospective data of patients from CHUV and 25 from Tanzania, ie, randomly selected 50% among hospital or study patients). CHUV patients necessitating a TDM intervention often present an overly complex clinical situation, allowing for report-generation testing in extraordinary cases. Experienced pharmacologists will generate a manual report using the GUI of Tucuxi to individualize the therapy of the selected patients. Such a “standard” document will contain all the essential information to justify the chosen dosage adjustment, including the patient clinical situation, data nonreliability, or inconsistencies. It will serve as the gold standard for the TuberXpert report, which will be compared to it to identify any discrepancies. We will verify the correctness of the provided guidance and the presence of all the necessary clinical information, justifications, and warnings. This step will also allow for the refinement of the report to guarantee the reliability of the information for the final user, that is, a clinician without strong TDM expertise. Before conducting this project phase, we will elaborate a detailed protocol to ensure the most reliable validation.

After this first validation step, we will update the CDSS and the report generation based on the study results and specifically on the feedback of the pharmacologists. Indeed, the CDSS development will be driven by the use cases defined in the project beginning, while the validation will be conducted on another set of retrospective data. As such, some adjustments will likely be required.

After the software update, we will conduct a second validation, following the same protocol but on another set of patients (25 from Tanzania and 15 from CHUV). This second step should end with very few differences between the pharmacologists’ outputs and the generated reports, and we only expect minor software modifications to be necessary after that. Finally, we will again run TuberXpert against all the use cases to validate it against the pharmacologists’ choices made during the 2 validation steps. The research question component is—is the CDSS developed reliable enough in comparison with a human pharmacologist?

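### The round 2 reference reports are written after the pharmacologists have given feedback on round 1, so round 2 agreement may overstate how well the CDSS matches an independent expert

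*Protocol article*

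**What the plan says.** The System Validation section of the protocol article sets out the following sequence.

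- **Reference.** "Experienced pharmacologists will generate a manual report using the GUI of Tucuxi to individualize the therapy of the selected patients". On the role of that document: "It will serve as the gold standard for the TuberXpert report, which will be compared to it to identify any discrepancies".
- **Comparison.** "We will verify the correctness of the provided guidance and the presence of all the necessary clinical information, justifications, and warnings". The article does not say who makes the comparison.
- **Update.** After round 1, "we will update the CDSS and the report generation based on the study results and specifically on the feedback of the pharmacologists".
- **Round 2.** Once the software has been updated, "we will conduct a second validation, following the same protocol but on another set of patients". The set is 25 Tanzanian and 15 CHUV patients.
- **Expectation.** "This second step should end with very few differences" between the pharmacologists and the generated reports, with only minor modifications foreseen afterwards.
- **Final run.** TuberXpert is run again on all use cases and checked against the pharmacologists' "choices made during the 2 validation steps".

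The research question for this phase is whether the CDSS is reliable enough when set against a human pharmacologist. The section also says that a detailed protocol for this phase will be written beforehand. That protocol is not shown.

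**The concern.** A reference standard should not depend on the system under test. Here the reference is expert judgement, and the experts' feedback on the system comes between the two rounds. An expert who has seen how TuberXpert reasons about a dose, words its sentences and triggers its warnings can carry those conventions into later reports, even for different patients. Some agreement in round 2 could then come from the experts having moved rather than from the software being right.

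Round 2 carries most of the weight of the reliability claim. Round 1 cases drive the update, and the final run reuses cases from both rounds. The later field phase compares CDSS output with treating clinicians' decisions, not with pharmacologists' reference reports. Round 2 is therefore the only check of the updated CDSS against pharmacologists on cases that did not shape the update, and it comes before use in clinics.

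**Working it through.** The article gives no agreement threshold, rate or error figure for this phase, so there is no figure to reproduce. The check is on the order of the steps.

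**1. Is the round 2 reference written after the feedback?** Yes. Round 2 starts only after the update, and the update rests in part on the pharmacologists' feedback. Repeating the same protocol on new patients means writing new manual reports, because that is how the protocol creates its reference.

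**2. Had the pharmacologists seen TuberXpert output by then?** This is a strong inference, not a statement. Feedback that leads to changes in the CDSS and its reports must concern its output or its discrepancies from the manual reports. The text does not say how many reports any one expert read.

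**3. Are the report writers the same people in both rounds?** The article speaks of the pharmacologists as one group across both steps and mentions no new writers. This suggests the same individuals but does not fix it.

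**4. Is there another check that does not share the problem?** Only in part.

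| Check | Reference written before the feedback? | Cases independent of the update? |
|---|---|---|
| Round 1 | Yes | No, they drive it |
| Round 2 | No | Yes |
| Final run, round 1 cases | Yes | No |
| Final run, round 2 cases | No | Not fully, since minor changes may follow round 2 |

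No row has Yes in both columns.

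**5. What could this do to the result?** The article does not allow the size to be derived. The following only shows the mechanism, and both rates are assumptions without support in the document.

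- Round 2 size: 25 + 15 = 40 cases.
- Assume that an unexposed expert would differ from the CDSS in 20% of cases: 0.20 × 40 = 8.
- Let d be the share of those cases in which an exposed expert has adopted the CDSS position. Observed differences = 8 × (1 − d).
- d = 0: 8 of 40 (20%).
- d = 0.25: 8 × 0.75 = 6 of 40 (15%).
- d = 0.50: 8 × 0.50 = 4 of 40 (10%).

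The software is identical in all three lines. If the experts do not move, there is no bias. If they become stricter, the count goes up rather than down.

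**The case against.** The strongest reply is that this is a condensed article which promises a detailed protocol for the phase. Who writes the reports, who is blinded and when the reports are written are matters for that protocol, and the article rules out no safeguard. This stands as far as missing blinding detail goes: its absence here is not an error. It does not fully answer the point, because the article itself sets the sequence of reference, feedback, update and new reference. The promised protocol is the right place to change it.

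Other parts of the reply also stand:

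- Round 2 uses different patients, and nothing suggests that an expert sees the CDSS report for a case before writing the manual one. This limits the risk, but rules and report conventions carry over between cases.
- The only movement the article describes is the software following the experts. Experts who have seen software errors may also become more demanding, so the direction is not certain.
- Experts meet the system's logic before round 1. They use the Tucuxi interface for the manual reports, CHUV pharmacologists choose among Tucuxi's proposals in the model validation, and expert pharmacologists take part in the report-design interviews. Earlier locking removes only the further exposure between rounds.

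A reader might infer that the report writers have studied all 25 or more round 1 TuberXpert reports. The article credits the pharmacologists only with feedback and leaves the comparison to an unspecified group. A reader might also infer that the plan takes a fall in differences from round 1 to round 2 as proof that the update worked. It does not: it states an expectation for round 2 and defines no contrast between rounds as an endpoint.

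**Conclusion.** The point holds in conditional form. The sequence is fixed in the article: the round 2 reference reports follow the pharmacologists' feedback on round 1, and no unexposed report writers are mentioned. Two links are inferred: that the writers saw TuberXpert output, which is very likely, and that the same people write both sets, which the wording suggests. If both are true, round 2 agreement may overstate reliability against an independent pharmacologist. The more likely direction favours the CDSS, but the documents do not support saying that it always does.

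The size is unknown, and the illustrative counts are not an estimate for this study. The level of round 2 agreement is affected whether or not it is compared with round 1. The change is worth making because it closes this route of bias at almost no cost.

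**What to change.** In the detailed validation protocol, fix this order of work:

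1. Select both validation sets at the outset: 25 + 25 = 50 Tanzanian cases and all CHUV cases for both rounds.
2. Have all manual reports written, dated and locked before any report writer sees TuberXpert output.
3. Compare set 1 with its locked reports, collect the pharmacologists' feedback and update the software.
4. Compare set 2 with the reports already locked.

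The feedback loop stays intact, and the reference is protected from TuberXpert output whether or not the same experts write both sets.

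**Cost.** The number of manual reports does not change, but the experts' work falls earlier. The order is feasible if the set 2 cases are retrospective like those of set 1, as the shared protocol implies, and if the rifampicin model is settled before this phase, as the article states. A later change to the model or the exposure target would mean revisiting the locked reports.

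**What it does not solve.** Exposure through the Tucuxi interface and the report-design work remains and should be stated as a limitation.

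### The final validation run reuses cases that prompted the software edits, so it is a regression test; first-pass round-2 agreement is the usable reliability estimate

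*Protocol article*

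**What the plan says.** All of this is in the System Validation section of the protocol article unless noted.

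- **Standard.** Experienced pharmacologists write a manual report for each selected patient. That report is the gold standard for the automated one.
- **Round 1.** Retrospective CHUV patients (number not given) and "25 from Tanzania, ie, randomly selected 50% among hospital or study patients". Afterwards "we will update the CDSS and the report generation based on the study results and specifically on the feedback of the pharmacologists".
- **Round 2.** A second validation "following the same protocol but on another set of patients (25 from Tanzania and 15 from CHUV"). The authors look for very few differences here, and "we only expect minor software modifications to be necessary after that".
- **Final run.** After that, "we will again run TuberXpert against all the use cases to validate it against the" choices that the pharmacologists made in the two rounds. No further patients are mentioned.
- **Question to be answered.** The section closes by asking whether the CDSS is reliable enough when set against a human pharmacologist.
- **Next step (Implementation in the Field).** Before clinicians receive the tool, the CDSS is run on field patients without affecting their treatment, and its output is compared with the clinicians' own decisions. Training and live use follow.

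**The concern.** A validation result should estimate how the software will perform on cases it has not met. In the final run, the software has just been edited in response to disagreements on these very cases, and the reference answers were known when the edits were made. High agreement would show that the edits worked and broke nothing else. It would say little about the next patient.

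The software is to give dosing guidance to clinicians without strong TDM expertise. If the final run is cited as evidence of reliability, the disagreement rate with experts will look lower than the data can support, and the version that goes to the field will be credited with a test it did not have.

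**Working it through.** The article gives no sample size, power or precision figure for the validation, so there is no stated result to reproduce. The one arithmetic link is consistent: 50% of the 50 Tanzanian study patients is 25, which matches the two Tanzanian sets of 25.

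**Step 1: what each stage adds**

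| Stage | Version tested | New patients | Comparator |
|---|---|---|---|
| Round 1 | As developed | 25 Tanzania + unstated CHUV number | Pharmacologists |
| Round 2 | After round-1 edits | 25 Tanzania + 15 CHUV = 40 | Pharmacologists |
| Final run | After round-2 edits | 0 | Pharmacologists' choices already made |
| Silent field phase | Presumably the version after the final run | Number not given (cohort of at least 30, not split by phase) | Clinicians' decisions under standard management |

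The version edited after round 2 has no row with both new patients and the expert comparator.

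**Step 2: direction of the bias.** Suppose, as an assumption, that round 2 shows 2 discrepancies in 40 and both are then edited away. The first-pass rate is 2/40 = 5%, with an exact (Clopper-Pearson) one-sided 95% upper limit of 14.9%. The rerun on the same 40 would show 0 of 40 whatever the true rate in new patients, provided the edits do what they were written to do.

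**Step 3: what round 2 can support.** With zero discrepancies in n cases, the one-sided 95% upper limit is 1 − 0.05^(1/n).

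- n = 40: 1 − 0.05^(1/40) = 7.2%
- n = 25 (Tanzanian cases only): 1 − 0.05^(1/25) = 11.3%

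These limits apply to the version that entered round 2, before any later edit. The zero counts are assumptions for scale.

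**Step 4: what fresh cases would reveal.** The chance that n new patients show at least one discrepancy is 1 − (1 − p)^n. The true rates p are assumed.

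| p | n = 40 |
|---|---|
| 2% | 55% |
| 5% | 87% |
| 10% | 99% |

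Round 2 offers this sensitivity for errors in the round-1 update. For a new error introduced after round 2 that shows only in cases unlike those already used, the final run offers none.

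**The case against.** Several stronger readings are tempting, and the article does not support them.

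- *A reader might infer that post-round-2 changes reach patients with no independent check.* The silent field phase uses new patients and comes before live use, so this is wrong. What remains is that its stated comparator is standard practice. A disagreement there cannot tell a CDSS error from a usual-practice decision that an expert would also have changed.
- *A reader might infer that the software is judged on its own training cases after round 1 too.* It is not: round 2 uses other patients and is a fair test of the round-1 update.
- *A reader might see a contradiction in the choice of validation cases.* The section says "We will assess the correctness of the generated reports based on use cases designed within the project among patients on rifampicin followed at CHUV", and the CDSS section says "We will carefully analyze every patient and use case scenario to design a formal decision tree", which could suggest that the development cases are reused. But System Validation also separates the two sets: development follows the use cases, "while the validation will be conducted on another set of retrospective data". This is loose wording, not a contradiction.
- *A reader might object that very few differences is no acceptance criterion.* The article promises a detailed validation protocol before this phase, and a numerical limit can properly sit there.
- *A reader might assume that all cases will be pooled into one near-perfect figure.* The article does not propose this, nor does it say that the final run alone answers the reliability question.

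It is also fair that the authors expect only minor edits after round 2. That limits the likely harm, but it is an expectation about a result not yet seen.

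What survives is narrow. The sequence, and the description of the last run as validation, are already fixed in the article and are not details left to a later document.

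**Conclusion.** The point holds in this limited form. The final run is a regression test described as validation, and its agreement is biased upward. Round 2, before any edit, is the last comparison with the pharmacologist standard on patients new to the software. The post-round-2 version has no such comparison, and the silent field phase is a real but different check.

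On size, a flawless first pass in round 2 would still leave a discrepancy rate of up to 7.2% compatible with the data overall, and up to 11.3% in Tanzanian cases. Both figures rest on an assumed zero count, on independent cases, and on one yes/no discrepancy per case. The bias in the final run itself cannot be quantified from the article, because it depends on how many discrepancies are found and edited away.

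**What to change.** In the validation protocol that is still to be written:

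1. Freeze the software version before round 2. Report its first-pass agreement on the 40 round-2 patients, before any edit, as the validation result. Give an exact confidence limit and show the 25 Tanzanian cases separately.
2. Call the final run a regression test and do not cite it as evidence of reliability.
3. State that any change to dosing or alert logic made after round 2 has not been validated against experts on new cases.
4. Optionally, obtain pharmacologist reports on the silent-phase patients. This would compare the fielded version with the expert standard on new cases before live use.

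Items 1 to 3 need wording and a version freeze, with no new patients; the downside is a less favourable headline figure. Item 4 needs some extra expert time, since no pharmacologist reports are described for those patients.
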